## Introduction

### Background

Yoga has been shown to reduce pain and improve function in populations with chronic low back pain (CLBP) in multiple randomized controlled trials (RCTs) [1,2]. However, results vary, and effects are generally modest [3]. This variation is perhaps due to differences in the specific neurobiological mechanisms through which yoga exerts clinical improvements on pain that are affected by different yoga interventions. These mechanisms, which have been only minimally identified, could potentially be harnessed to achieve more consistent and optimal outcomes from yoga interventions. A study that examined mediators of yoga’s effects on pain lacked strong theoretical bases for assessment of the mechanisms involved [4]. Using a comprehensive theoretical emotion regulation (ER) model of yoga [5], we will conduct the first test of ER as a primary mechanism of yoga’s effects on CLBP. We will also test the role of pain sensitization using somatosensory and gene expression profiles in this model [6] and examine the specific aspects of ER.

ER refers to “extrinsic and intrinsic processes responsible for monitoring, evaluating, and modifying emotional reactions, especially their intensive and temporal features, to accomplish one’s goals” [7]. Emotions strongly influence perceptions of pain intensity and predict disability [8], particularly among individuals with CLBP [9,10]. Interventions that promote adaptive ER skills reduce pain in patients with chronic pain [11]. Increasing evidence demonstrates that consistent yoga practice can promote improved ER [12,13], but research has not yet tested whether the effects of yoga practice on CLBP are due to improvements in ER.

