### Statistical Analysis

The primary aim of this study will test the null hypothesis that the 2 population means are equal between the yoga and stretching and strengthening groups on the primary outcome, pain severity as measured by the BPI-SF, as well as the primary MOA, ER as assessed by the DERS. Power calculations incorporated prior effect sizes from works by others. A proposed sample size of 102 per group, which adjusted for attrition, was calculated to detect statistically significant results with 80% power (estimated *d*=0.50). In consideration of our secondary aims, we also powered the detection of paths a and b within pain interference mediation models. This was done using simulation in R (R Foundation for Statistical Computing; N=5000). Following simulation methods (N=5000) presented in Fritz and MacKinnon [76], sample size was determined by increasing simulation sample size until 90% of simulations significantly detected both paths a and b with estimated effect size magnitudes of *d*=0.39 (path a) and *d*=0.26 (path b) at α=.05. A proposed sample size of 116 was calculated, which was already reached when powering our primary aim.

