### Data Analysis

All analyses will be performed in SPSS (version 29; IBM Corp). A *P* value of .05 or less will be considered statistically significant. The primary outcome is pain severity (BPI-SF) and the primary MOA is ER (DERS). We will examine baseline demographics and study variables descriptively and test for differences between yoga and stretching and strengthening groups. If assumptions are met, a series of 2-sided *t* tests, mixed effects models, and path analyses will test our hypotheses. A mediation path analysis will be conducted examining the indirect path of group and change in ER from baseline to 6 weeks (path a), and change in ER from baseline to 6 weeks and pain severity (BPI-SF) at 12 weeks (path b) controlling for baseline pain severity. The magnitude of indirect path b will be assessed controlling for path a and the direct path between group and change in pain severity at 12 weeks (path c) to test if changes in ER predict subsequent changes in pain severity. Identical models will be created with change in ER from baseline to 12 weeks and pain severity at 3- and 6-month follow-ups. The magnitude of indirect path b will be compared between groups to test if the path between ER and pain severity is greater in the yoga group than in the stretching and strengthening group. If 95% CIs of path estimates do not contain 0, they will be considered meaningful. Finally, a series of moderated mediation path analyses will be conducted, examining the measures of baseline pain sensitivity (QST scores and normalized gene expression values), strength and flexibility, pain interference, and quality of life as moderators of the identical mediation model. All analyses will also be adjusted for important covariates including, but not limited to demographics (eg, biological sex, race, and sex), cohort, instructor, and intervention components (Essential Properties of Yoga Questionnaire) and credibility or perception of success (Credibility Expectancy Questionnaire). Sensitivity analyses will examine whether treatment responders and nonresponders differ significantly in baseline ER abilities. Baseline DERS scores will also be examined as a continuous moderator in main study analyses to establish whether some individuals may enjoy greater benefit from this intervention more than others.

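### Path b uses the raw change in emotion regulation without naming baseline DERS as a covariate, so it can mix baseline level with change

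*Protocol article*

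**What the plan says.** In the Protocol article, Data Analysis, path a runs from group to the change in ER between baseline and 6 weeks. Path b is "change in ER from baseline to 6 weeks and pain severity (BPI-SF) at 12 weeks (path b) controlling for baseline pain severity". Path b is to be assessed with group in the model, "to test if changes in ER predict subsequent changes in pain severity". The same form is carried forward: "Identical models will be created with change in ER from baseline to 12 weeks and pain severity at 3- and 6-month follow-ups". The moderated mediation analyses reuse it again. A path counts as meaningful when its 95% CI excludes 0, whatever its direction.

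Two other sentences in that section bear on baseline DERS. The covariate sentence is open-ended: "All analyses will also be adjusted for important covariates including, but not limited to demographics". It goes on to name cohort, instructor, intervention components and credibility, but not baseline DERS. The last sentence gives baseline DERS a different role: "Baseline DERS scores will also be examined as a continuous moderator in main study analyses", in order to see who benefits more.

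**The concern.** The change score DERS6 − DERS0 contains −DERS0. People with poor ER at baseline therefore tend to show larger falls, through regression to the mean alone. If baseline ER is related to 12-week pain beyond what baseline pain explains, and that relation is not the exact mirror image of the 6-week relation, the coefficient of the change score absorbs part of it. Randomisation does not protect against this, because the mediator is not randomised.

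The Background section gives some reason to expect a relation with level: "Emotions strongly influence perceptions of pain intensity and predict disability". It gives no figure, and it does not speak to what remains after adjusting for baseline pain.

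Path b carries the trial's main mechanistic conclusion. An attenuated path b could miss a real mechanism. A path contaminated by baseline level could be called meaningful when 6-week ER has no effect on later pain.

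**Working it through.** **Inputs from the article.** N=204; α=0.05; path effect sizes from the Statistical Analysis section, "estimated effect size magnitudes of *d*=0.39 (path a) and *d*=0.26 (path b) at α=.05". The article labels these as d and states them for pain interference models. Here 0.26 is borrowed for pain severity and read as a standardised coefficient.

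**Inputs that are assumptions.** The article gives no DERS SD, no between-visit correlation and no DERS-pain correlation. Assumed: visit correlation ρ=0.7; equal DERS SDs; baseline DERS-pain correlation r=0.3; slope of 12-week on baseline pain 0.5; residual SD 0.8.

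**The plan's own figure.** The article gives no power figure for the pain severity mediation model. Its sample size of 116 for 90% power on both paths belongs to the pain interference models. It did not reproduce: joint power at 116 was about 76% with 0.39 read as a regression coefficient, and 42% with it read as a group difference. That is a separate matter and nothing below depends on it.

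**Step 1, algebra.** Let pain12 = b·DERS6 + g·DERS0 + c·pain0 + error, and D = DERS6 − DERS0. Then

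pain12 = b·D + (b+g)·DERS0 + c·pain0 + error.

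With DERS0 in the model, the coefficient of D is b, whatever g is. Without it, the coefficient of D is b + (b+g)·λ, where λ is the slope of DERS0 on D given pain0 and group. With equal SDs,

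λ = −(1−r²) / [2 − (1−ρ)r²].

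At r=0 this is −1/2, so the coefficient is (b−g)/2. At r=0.3 and ρ=0.7, λ = −0.91/1.973 = −0.461.

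**Step 2, numbers** (b=0.26 where 6-week ER has an effect; power from repeated simulation at N=204):

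| What drives 12-week pain | g | Path b as written | Power as written | Power with DERS0 |
|---|---|---|---|---|
| ER level at 6 weeks | 0 | 0.26 − 0.26×0.461 = 0.14 | 44–45% | 90% |
| Intermediate | −0.13 | 0.26 − 0.13×0.461 = 0.20 | 74–76% | 88–90% |
| Change itself | −0.26 | 0.26 − 0 = 0.26 | 93–94% | 89–90% |

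With DERS0 added, the estimate is 0.26 in all three rows.

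Hand check of the first row, with DERS0: SE ≈ 0.8/√(204×(1−0.7²)) = 0.8/√104.04 = 0.078, and 0.26/0.078 ≈ 3.3, which gives power of about 90%.

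**Step 3, only baseline ER matters** (b=0, baseline slope g of 0.20 to 0.30). The coefficient of D is −0.461×g, that is −0.09 to −0.14. Simulation at N=204 rejects 23–43% of the time, nearly always with the sign opposite to the hypothesis, against 4–6% with DERS0. Over visit correlations of 0.5 to 0.8 and N of 174 or 204, rejection runs from about 14% to just over 60%.

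**Step 4, sensitivity of the attenuation.** Share of b recovered without DERS0 if level drives pain (g=0):
- equal SDs, r from 0 to 0.5: 0.50 to 0.62;
- 6-week SD 0.8 of baseline, r=0.3, ρ from 0.4 to 0.8: 0.35 falling to 0.06 (at ρ=0.7, 0.203×0.26 = 0.05);
- 6-week SD 1.2 of baseline, same range: 0.68 rising to 0.93 (at ρ=0.7, 0.808×0.26 = 0.21).

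If baseline ER adds in the same direction (g=+b/2), the share with equal SDs is 0.25 to 0.43.

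**The case against.** The strongest reply is that the protocol's hypothesis concerns change, and the abstract also defines the mechanism as change in DERS. If pain depends on change alone, the model as written is unbiased and slightly more powerful than the adjusted one. This stands, and it rules out an unconditional claim of bias. It does not make the adjustment wrong, because the adjusted model recovers the same coefficient in that case too. Nor does the article commit itself to the pure-change case: the section on the primary MOA names the DERS score at 12 weeks.

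A reader might infer that the plan roughly halves the ER effect. The documents do not support that as a general statement. It needs a level-driven effect and similar DERS SDs at the two visits, and the article supplies neither. The 0.26 is itself borrowed from the pain interference models.

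A reader might also infer that baseline DERS is excluded. It is not: the covariate list is open, and a moderator model would normally carry the main effect of baseline DERS. But an unnamed possible covariate is not a specified one, and the moderator analysis answers a different question from the main mediation test.

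The scenario in which only baseline ER matters uses slopes with no source in the article. Its spurious paths would mostly contradict the proposed mechanism, not falsely support it. It shows what can happen, not what is likely.

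Path a is not biased, because group is randomised.

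**Conclusion.** The point holds in conditional form. The article fixes path b as a raw change score with baseline pain as the only baseline score named, and no other sentence commits baseline DERS to the main mediation model. The coefficient then isolates the ER effect only under an exact equal-and-opposite restriction that the article does not justify.

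Under the stated assumptions, path b ranges from about 0.14 (level drives pain) through 0.20 (intermediate) to an unbiased 0.26 (change drives pain). Power at N=204 is about 45%, 75% and 94%, against about 90% with baseline DERS in each case. Unequal DERS SDs move the level-driven figure to between 0.05 and 0.21 at a visit correlation of 0.7. The direction of the problem is clear, but its size cannot be fixed from the article.

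**What to change.** State that baseline DERS is a covariate in the path b equation of every mediation model: 6-week ER to 12-week pain, 12-week ER to 3- and 6-month pain, and all moderated versions. In the first model this is pain12 ~ group + DERS6 + DERS0 + pain0 plus the planned covariates. With DERS0 present, the change score and the 6-week score give the same path b, so the change-score wording can stay. Add baseline DERS to the path a equation as well, for precision only. Settle this before the mediation analyses are run.

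The cost is a sentence of analysis text and one degree of freedom per equation. No new data are needed, since DERS is already measured at baseline. If pain depends purely on change, about 4 points of power are lost (roughly 94% to 90% at N=204).

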**Conclusions:**

The study will provide important data for evaluating whether improvements in ER are responsible for reduced pain perception and pain sensitivity as well as increased quality of life in the context of chronic pain. The study findings have important implications for determining the mechanism of action for yoga and possibly other mind-body interventions as nonpharmacological therapies for pain management. The results of the study will inform the content, delivery, and measures for intervention trials involving yoga as a modality for relieving pain and improving function.

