#### Interventions

All yoga and stretching and strengthening sessions will take place on a secure web-based platform. This delivery modality will provide more inclusive participation and reduce barriers such as participant transportation and parking. For both study arms, 75-minute classes will be offered 3 times per week for 12 weeks. Participants will be asked to attend at least 2 out of 3 of the offered classes per week. The importance of attending 2 sessions per week is emphasized during the first session and throughout all subsequent sessions. Participants who repeatedly miss sessions without notifying the study personnel will be contacted to check on the reason for nonattendance and to encourage resuming participation as soon as possible. Participants are encouraged to consult with the instructor individually before or after class about problems or difficulties they are encountering at home or in the formal sessions.

Participants are asked to practice exercises at home on days they do not attend formal synchronous sessions to maximize the benefit of the intervention. Participants will be emailed daily links to prerecorded practice videos that are approximately 25 minutes in length and asked to record the amount of time they spent on the practice videos.

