### Exploratory Variables

Demographics, class attendance or home practice, expectancies, and substance use will be measured to examine the impact on the primary and secondary outcomes. A brief questionnaire (minimum data set as recommended by the National Institutes of Health Taskforce on Research Standards for CLBP) [54] will assess demographics (age, gender, race or ethnicity, education, and employment status) and medical or psychiatric history (comorbidities, medication usage, and ongoing treatments). Attendance at yoga or stretching sessions will be assessed using attendance data from the session recordings. The Essential Properties of Yoga Questionnaire [72] will be used to rate both interventions (yoga and stretching or strengthening) and measures the extent to which 14 different dimensions are emphasized in a mind-body intervention (eg, physical challenge, breathwork, restorative postures, and mindfulness). The Credibility Expectancy Questionnaire [73], a 6-item self-report instrument, will be used to assess treatment credibility and patient expectancy for improvement [74]. In order to assess participants’ use of tobacco, alcohol, prescription medicines, cannabis, and other nonprescribed substances, the Alcohol, Smoking, and Substance Involvement Screening Test [75] will be administered by study staff at each time point.

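### Path b is an observational association: the named covariates omit baseline psychological state and practice dose, and nothing tests how much residual ER–pain confounding would overturn it

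*Protocol article*

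**What the plan says.** The Data Analysis section of the protocol article relates arm to ER change from baseline to 6 weeks (path a), and that change to "pain severity (BPI-SF) at 12 weeks (path b) controlling for baseline pain severity". Arm stays in the second equation: "The magnitude of indirect path b will be assessed controlling for path a and the direct path between group and change in pain severity". The same structure is reused for 12-week ER change and pain at the 3- and 6-month follow-ups. A path estimate whose 95% interval excludes 0 counts as meaningful.

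A general clause follows: "All analyses will also be adjusted for important covariates including, but not limited to demographics". The other named items are "cohort, instructor, and intervention components (Essential Properties of Yoga Questionnaire) and credibility or perception of success".

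Practice dose appears elsewhere. Under Exploratory Variables, "class attendance or home practice, expectancies, and substance use will be measured to examine the impact on the primary and secondary outcomes", and "Attendance at yoga or stretching sessions will be assessed using attendance data from the session recordings". Under Interventions, participants are "asked to record the amount of time they spent on the practice videos". The abstract's Conclusions give the purpose as "evaluating whether improvements in ER are responsible for reduced pain perception and pain sensitivity", and the Discussion repeats this aim for reduced pain.

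**The concern.** Randomisation protects path a and the total effect. It does not protect path b, because participants within an arm are not allocated to gain more or less ER. Anything that drives both ER gain and pain relief will appear as path b.

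The article itself makes practice dose a plausible candidate. Dose varies between people: three classes a week are offered, at least two are asked for, and home practice is encouraged to maximise benefit. The section on the integrative model says that physical activity alone can improve ER. The section on strength and flexibility says that these may mediate part of yoga's effect on pain, which is a route from practice to pain that bypasses ER. Strength and flexibility enter the analysis only as moderators. Baseline emotional state is a second candidate.

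The covariates that are named do not fill the gap. The Essential Properties of Yoga Questionnaire rates the content of the interventions, and the credibility questionnaire measures expectancy. Neither records how much an individual practised. At stake is the trial's central mechanistic conclusion.

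**Working it through.** **Plan's own figure.** No figure in the plan is disputed here. The nearest benchmark is the planned path b of 0.26 in Statistical Analysis, which was set for the pain interference models. It serves below as a yardstick only.

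**Inputs from the article.** N = 204, α = .05 (taken as two-sided), planned path a = 0.39 (taken as a two-group standardised difference), arm and baseline pain in the model.

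**Assumed inputs.** The article does not say how strongly dose relates to ER change or to pain. A standardised coefficient g from 0.1 to 0.5 is assumed on both legs. Baseline pain is assumed to have coefficient 0.5 on 12-week pain. The true effect of ER on pain is zero. Signs are set so that all effects are positive.

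**Model.** With arm G, dose U and baseline pain B, all except G standardised:

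- ER change: M = 0.39·G + g·U + error, with variance 1 given G
- Pain relief: Y = 0.5·B + g·U + error, with variance 0.75 given B
- Fitted: Y on G, B and M, with U omitted

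**Spurious slope.** Given G and B, cov(M, Y) = g·g and var(M) = 1, so the expected path b is g².

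**False-positive rate.** SE ≈ √[(0.75 − g⁴)/200]. For g = 0.3, SE = √(0.7419/200) = 0.061, z = 0.09/0.061 = 1.48, and the rejection rate is about P(Z > 1.96 − 1.48) ≈ 32%. Simulation agrees:

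| g on both legs | Spurious b | Path b significant, N = 204 | Paths a and b both significant, N = 204 |
|---|---|---|---|
| 0.1 | 0.01 | 5–6% | 4% |
| 0.2 | 0.04 | 10% | 8% |
| 0.3 | 0.09 | 32% | 23–25% |
| 0.4 | 0.16 | 75% | 60% |
| 0.5 | 0.25 | 99% | 78% |

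The last column is close to the path b rate times the power for path a, about 0.79 at N = 204. It assumes that yoga truly improves ER by 0.39. If the arms do not differ in ER, the joint rate stays at about 5% or less for every g shown.

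**Fewer participants.** With 128 analysed, the path b rates for g = 0.1 to 0.4 are about 5%, 8%, 20% and 55%.

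**Effect of adjusting for dose (N = 204).** If dose is measured without error, path b rejection returns to about 5%. With reliability 0.7 it is about 4%, 6%, 7%, 15% and 35% for g = 0.1 to 0.5. Adjustment helps but is incomplete when confounding is strong and self-report is noisy.

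**Residual correlation that nullifies b = 0.26.** With unit error variances and no other covariates it is 0.26/√(1 + 0.26²) = 0.25. If baseline pain leaves outcome variance 0.75, it is 0.26/√0.75 = 0.30. A residual ER–pain correlation of roughly 0.25 to 0.30 would therefore account for the whole planned path.

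**The case against.** **Other covariates are held fixed.** A reader might infer that path b adjusts for baseline pain alone. That is not so: arm and the named covariates are also in the model.

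**Dose is not excluded.** The covariate list is open. Demographics and expectancies stand beside dose under Exploratory Variables, and both reappear as covariates. The final list may be settled in an analysis plan that is not shown. Dose is therefore unnamed rather than ruled out. What remains is that the article fixes the model and the interval rule while leaving these confounders unnamed.

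**Psychological measures are not ignored.** Baseline DERS and quality of life are listed as moderators. That is not the same as adjusting the main path b equation for them.

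**The plan has safeguards.** A positive indirect effect also needs the randomised path a. The plan also compares path b between arms, and confounding that acts alike in both arms leaves that comparison at about 5% error. Both points stand and limit the damage. Neither protects the path b estimate itself.

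**No causal conclusion has been drawn.** A reader might infer that the plan already declares ER responsible for pain relief. It says only that it will evaluate whether this is so.

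**The size is assumed.** No figure in the article supports any value of g, and equal links on both legs is a simplification. At 0.1 the distortion is negligible.

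**Dose follows randomisation.** It may depend on arm, early ER gain or early pain relief, so adjusting for it changes what the direct and indirect effects mean. This rules dose out of the main model but not out of a sensitivity analysis.

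**Conclusion.** The concern holds in limited form. Path b is observational, its named covariates include neither a baseline psychological measure nor individual practice dose, and the decision rule has no check on residual ER–pain confounding. ER could be credited wrongly; the documents do not support saying that it would be. The problem is negligible for common-cause links near 0.1, modest at 0.2 and serious from about 0.3. A spurious slope close to the planned 0.26 needs links of about 0.5 on both legs. These sizes rest on the assumed linear model, equal links and no true ER effect. The change is worth making because the mechanism question turns on this path and the data are already collected.

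**What to change.** 1. Add baseline SF-36 emotional well-being to the path b equation.
2. For each mediation result, report the residual ER–pain correlation at which the indirect effect falls to zero. In the linear model without interaction this equals the partial correlation of ER change with the outcome given arm and the same covariates, so it needs no special software.
3. As a prespecified sensitivity analysis, not the main model, add classes attended and home-practice minutes up to the ER assessment (6 or 12 weeks, as the model requires) to the path b equation. State that dose is post-randomisation and may be affected by arm or early ER gain.
4. Describe ER as associated with pain relief unless the result survives these checks. Define survival before the data are unblinded: the interval still excludes 0 after steps 1 and 3, and the nullifying correlation exceeds a benchmark set and justified in advance.

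**Cost.** Analysis-plan wording and one standard sensitivity analysis, with no new data. Path b may become slightly less precise and less favourable. Self-reported home practice is imperfect, so step 3 removes only part of any confounding, and the direct and indirect effects mean something different in that model.

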**Objective:**

This study will test whether the effects of yoga on CLBP (improved pain severity and interference) are mediated by improved ER, the extent to which effects are related to specific aspects of ER, and the role of pain sensitization as a mediator or moderator of effects. In this study, pain sensitization will be assessed by quantitative sensory testing and gene expression profiles to examine whether pain sensitization moderates yoga’s effects on pain or whether yoga and ER abilities reduce pain sensitization, leading to decreased pain severity and interference.

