**Figure 1 figure1:**
[figure not shown]
Model of primary and alternative mechanisms of action. Model 1 proposes that pain sensitization moderates yoga’s effects on pain, in that chronic low back pain patients with higher sensitization may benefit less given that their pain is more centralized.

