### Pain Sensitivity May Influence the Effects of Yoga and ER on CLBP via Moderation or Mediation

Recent studies document that patients with CLBP demonstrate sensory and functional alterations reflecting peripheral and central nervous system sensitization associated with enhanced pain sensitivity [23-25]. Enhanced pain sensitivity as a mechanism of CLBP includes sensitization of nociceptors and neuronal circuits [26] and increased pain signaling through membrane excitability and synaptic efficacy [27], which are conferred through altered expression of pain sensitivity (and immune-related) genes [6,28]. The somatosensory changes associated with enhanced pain sensitivity in CLBP involve decreased thermal and mechanical pain thresholds at the site of pain and remote areas [25,26].

Preliminary research suggests that negative emotion is an important determinant of pain sensitivity [29,30], predicting up to 23% of the variance in CLBP-related disability [31,32]. For instance, greater pain catastrophizing and anxiety are associated with lower standardized values of heat pain threshold and tolerance in patients with chronic pain [33]. In turn, negative emotions and inability to tolerate stress have been shown to activate inflammatory pathways through the release of proinflammatory cytokines and substance P [34,35]. To date, only 2 small studies have examined whether yoga specifically influences pain sensitivity. However, in a systematic review of 15 RCTs, yoga was associated with decreases in interleukin-1β, interleukin-6, and tumor necrosis factor-α [36]. In addition, specific components of yoga (meditation, relaxation, and breathing) have been shown to alter gene expression profiles and levels of inflammatory mediators [37-39].

As shown in Figure 1, we propose that pain sensitization moderates yoga’s effects on pain, where patients with CLBP with higher sensitization may benefit less [40,41], given that their pain is more centralized [42,43]. This is a fairly novel hypothesis with some supportive evidence [44,45]. We will also explore the possibility that yoga and improved ER abilities might actually *improve* sensitization and thus decrease pain (Figure 2).

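### Model 1 says sensitization moderates yoga's effect on pain, but the only test named sits inside the emotion-regulation mediation model, where no single term measures that

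*Protocol article*

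**What the plan says.** The abstract's Objective sets out "to examine whether pain sensitization moderates yoga’s effects on pain or whether yoga and ER abilities reduce pain sensitization". The Introduction section on pain sensitivity puts it as a directional hypothesis: "we propose that pain sensitization moderates yoga’s effects on pain, where patients with CLBP with higher sensitization may benefit less". The Figure 1 caption (Model 1) repeats that "patients with higher sensitization may benefit less given that their pain is more centralized", and the Discussion states the same aim.

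Data Analysis is the only place that gives baseline sensitization an analysis as a moderator: "a series of moderated mediation path analyses will be conducted, examining the measures of baseline pain sensitivity (QST scores and normalized gene expression values"), together with other measures, "as moderators of the identical mediation model". In that model the mediator is measured after randomisation; path b is described as "change in ER from baseline to 6 weeks and pain severity (BPI-SF) at 12 weeks (path b) controlling for baseline pain severity". The text does not say whether path a, path b or the direct path is to be moderated. The abstract and the Results section likewise name only mediation and moderated mediation. Data Analysis also has a general sentence, "a series of 2-sided *t* tests, mixed effects models, and path analyses will test our hypotheses", which ties none of these methods to sensitization.

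**The concern.** Whether more sensitized patients get less pain relief from yoga is a question about the difference between arms in pain, at different levels of a baseline variable. Group is randomised and sensitization is measured beforehand, so a group by sensitization interaction on pain answers it with no assumption about ER.

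The named analysis estimates other quantities:

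- **Path a moderation** is a randomised comparison, but of ER change, not pain.
- **Path b moderation** is about how ER change relates to pain. It needs no unmeasured common cause of the two, which randomisation does not supply.
- **Direct-path moderation** is about the part of yoga's effect that remains after conditioning on ER change, and needs the same assumption.

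Because the path is not named, the conclusion on a stated objective can depend on which term is read. Moderation that runs outside ER can go unseen in an indirect-path test. Moderated mediation of pain can also be declared when pain benefit is the same at every level of sensitization.

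**Working it through.** **Inputs.** From Statistical Analysis: 102 per arm, so N = 204; path a = 0.39; path b = 0.26; alpha .05. The article gives no figure for the moderation test, so there is none to reproduce. The attrition rate is not stated, so the full 204 is used. Assumptions: sensitization W standardised; residual SDs of 1; the moderation slopes; and the loading L of one unmeasured cause on both ER change and 12-week pain.

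**Step 1: what each term is.** With G = group and M = ER change:

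- M = a0 + a1·G + a2·W + a3·G·W
- Y = c0 + c1·G + c2·W + c3·G·W + b·M

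Substituting M, the coefficient of G·W on pain without ER is **c3 + a3·b**. That sum is Model 1's quantity. Neither c3 nor a3·b alone equals it. If b also varies with W, this simple sum no longer holds.

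**Step 2: power at N = 204.** SE(G·W) is about residual SD × 2/√204 = 0.140 × residual SD. Without ER in the model, the residual SD of pain is √(1 + 0.26²) = 1.033, so the SE is 0.1447. SE(b) is about 1/√204 = 0.070. Power is about Φ(z − 1.96).

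- *Moderation −0.35, wholly outside ER.* Total effect: z = 0.35/0.1447 = 2.42, power 0.68. Direct path: 0.35/0.140 = 2.50, power 0.71. Indirect path: a3 = 0, so at most about 5%. Simulation: 68%, 70%, 5%.
- *Moderation −0.35, of which −0.10 via ER (−0.385 × 0.26) and −0.25 direct.* Total effect: about 66% by simulation. Direct path: 0.25/0.140 = 1.79, power 0.43; simulation 40-42%. Joint test of a3 and b: 0.385/0.140 = 2.75 (0.785) and 0.26/0.070 = 3.71 (0.96), product 0.75; simulation 73-74%.
- *Moderation −0.10, only via ER.* Total effect: 0.10/0.1447 = 0.69, power 0.10; simulation 11%. Joint test: 72-73%. The direct-path term averages zero.

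**Step 3: declaring moderated mediation when pain benefit does not vary.** Set b = 0, c3 = 0, a3 = −0.39, so the total interaction is 0 + (−0.39 × 0) = 0. The shared cause gives an apparent b of L²/(1 + L²).

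- L = 0.4: apparent b = 0.16/1.16 = 0.138, SE about 0.069, z = 1.99, P = 0.51. For a3: 0.39/(0.140 × √1.16) = 2.58, P = 0.73. Product 0.37.
- L = 0.5: apparent b = 0.25/1.25 = 0.20, z about 2.9, P = 0.83. For a3: 0.39/(0.140 × √1.25) = 2.49, P = 0.70. Product 0.58.

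Simulated rates of declaring moderated mediation (joint significance of a3 and b):

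| Loading | Unit-variance errors | Errors rescaled | Total-effect test |
|---|---|---|---|
| 0 | 4% | 4% | about 5% |
| 0.2 | 6% | 7% | about 5% |
| 0.3 | 15-17% | 18-19% | about 5% |
| 0.4 | 36% | 47-49% | about 5% |
| 0.5 | 56% | 74-75% | about 5% |

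**Step 4: the pieces are biased, the sum is not.** At L = 0.4 the indirect piece is −0.39 × 0.138 = −0.054. The direct term absorbs +0.054, and the sum returns to 0.

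**Step 5: other readings of the path.**

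- With a3 = +0.5, an offsetting direct interaction of +0.13 and loading 0.7, the direct-path test rejects in 41-42% of trials (average estimate about +0.30) and the total-effect test in 4.5%.
- With ER-pain confounding that itself varies with sensitization and no causal moderation, path-b moderation is declared in 26-67%, against 6-9% for the total-effect test.

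**The case against.** Four points count on the other side.

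1. A reader might infer that sensitization is tested only inside the mediation model. The documents do not establish that. Mixed effects models are listed generically, a group by baseline interaction is an ordinary use of one, and the full protocol and analysis plan are not shown. What stands is that the article *names* only moderated mediation. That is a choice of method, not an omitted detail. The fact that baseline DERS is assigned to the main analyses as a moderator adds little, since those analyses may include the mediation models.
2. A reader might infer that the plan gives up randomisation altogether. It does not. Path a remains a randomised comparison, and with path b unmoderated in a linear model the total interaction can be rebuilt from the path estimates. The text does not plan to do so.
3. The hypothesis is partly mechanistic. The Introduction heading speaks of the effects of both yoga and ER, and Objectives lists sensitization as mediator or moderator straight after mediation by ER. Moderated mediation therefore answers a question the trial asks. It does not answer the one stated in the abstract, the Figure 1 caption and the Discussion.
4. The named method is not uniformly worse. When moderation runs through ER, the joint test is far more powerful (72-73% against 11%). When moderation lies outside ER, a direct-path interaction finds it as often as the total-effect test (70% against 68%), if that path is the one moderated. In Step 3 sensitization really does alter ER gain; the error is a spurious path b, the ordinary hazard of any mediation analysis.

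**Conclusion.** The point holds as a mismatch between a stated hypothesis and the analysis named for it. The article does not show that sensitization effects will be falsely declared or missed. That depends on which path is read and on how strongly ER change and pain share an unmeasured cause, and the documents settle neither. With weak confounding (loadings up to 0.2) the false-declaration rate stays near 4-7%; it becomes serious at 0.4-0.5. The miss is serious when moderation lies outside ER and only the indirect path is tested. All these rates rest on assumed slopes and loadings, linear models and no loss from the 204. The primary comparison of arms is unaffected. The correction is still worth making, because the objective appears in the abstract and the Discussion.

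**What to change.** For each baseline sensitization measure, pre-specify the group by baseline-sensitization interaction in the 12-week BPI-SF model, adjusted for baseline BPI-SF and without ER change, as the test of Model 1. Report yoga's effect with confidence intervals at low, mean and high sensitization. Keep moderated mediation as a secondary mechanistic decomposition, state which path is moderated, and do not use it alone to conclude that sensitization moderates yoga's effect on pain.

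The cost is a paragraph of analysis-plan wording and one regression per measure on data already being collected. Results says analysis follows final data collection, so the change can be fixed before results are seen. The downside is limited power, which should be stated: about 66% for -0.35 SD per SD at N = 204, and about 11% if moderation of -0.10 runs only through ER. Attrition lowers it further; for an assumed -0.5 outside ER, power falls from 92% at 204 to 75% at 128.
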